**3.3. Selection of STIs/BV for each objective**

See Appendix Table 3 for available STI/BV data in selected studies.

For objective 1, prevalence will be estimated for six STIs/BV (chlamydia, gonorrhea, syphilis, trichomoniasis, BV, and HSV-2) based on availability of data. For the majority of studies, HPV data were not available.

For objective 2, incidence will be estimated for five of the selected STIs (chlamydia, gonorrhea, syphilis, trichomoniasis, and HSV-2). BV was not included due to concerns about the accuracy of diagnostic criteria to assess incidence given the intervals between follow-up tests.

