**3.6. Stratification of prevalence and incidence estimates**

Because of possible heterogeneity in STI/BV prevalence and incidence among studies, for each STI/BV we plan to stratify results according to pre-specified characteristics. (See Supplemental Tables 1.1 – 1.2 for proposed stratifications for prevalence estimates and Supplemental Tables 2.1 – 2.2 for proposed stratifications of incidence estimates.) We will first stratify according to the study-level characteristics for region and population type. Within these strata (region and population type), we will then explore STI/BV prevalence and STI incidence according to individual-level characteristics, including: age, time period of enrolment, and pregnancy status (prevalence estimates only). Additional stratifications, such as by sexual behaviors including number of recent sexual partners, could be explored if resources allow. Additionally, diagnostic test used can influence observed prevalence. For BV, those diagnosed by Nugent or Ison-Hay criteria will be evaluated separately from those diagnosed by Amsel criteria only. A sensitivity analysis will be conducted to determine if the estimates remain robust if Amsel only results are included with the Nugent/Ison-Hay results (see section 5.3). For chlamydia, gonorrhea, syphilis and trichomoniasis, estimates will be evaluated by diagnostic test type to investigate robustness of estimates (see section 5.3).

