Region (based on geographical location of the study) will be defined as South Africa, Eastern Africa (Kenya, Uganda, Tanzania, Rwanda), or Southern Africa (Zambia, Zimbabwe, Malawi, Botswana). Population types (based on overall study population enrolled) will be defined as higher-risk or clinic/community-based populations. Higher-risk populations include studies where participants were recruited from bars or other recreational facilities like guesthouses and hotels, or were women who engage in transactional sex. Clinic/community-based populations include participants recruited in a clinic setting, such as a family planning/reproductive health clinic, as well as studies where participants were recruited from the general population or community. Some studies in the HC-HIV meta-analytic dataset recruited HIV-negative partners in HIV-discordant couples. Although these participants may be at higher risk for HIV transmission than the general population, their risk for STI/BV may be similar to clinic/community-based populations given that they are in a stable relationship. These studies will initially be analyzed separately, STI/BV specific estimates reviewed, and if appropriate (based on comparison with estimates from other populations), will be included in either the higher-risk strata or the clinic-based strata. If not appropriate, estimates from these studies will be presented separately. See Appendix Table 1 for proposed classifications of studies according to these two characteristics.

Time period, age, and pregnancy status will be based on individual participant characteristics. Time period will be categorized as participants whose baseline data were collected prior to 2002 (“earliest” time period), participants whose baseline data were collected during 2003 to 2006 (“later” time period), and participants whose baseline data were collected in 2007 or later (“latest” time period). The categorization of time periods may be adjusted if necessary based on available sample size. Age will be categorized as 15-49 years, 15-24 years, 25-49 years, and if possible given sample size, 15-19 years, and 20-24 years. The categorization of age may be adjusted if necessary based on available sample size. Pregnancy status will be based on pregnancy status at baseline, either self-reported or by pregnancy test.

To the extent possible given sample size, prevalence and incidence estimates will be cross-stratified by various characteristics.

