**5.3. Study limitations and sensitivity analyses**

Though this meta-analysis provides high quality individual participant data and valuable information about the prevalence and incidence of selected STIs/BV, our approach has some limitations. First, the validity of the results of the meta-analysis is dependent on the quality of the individual component studies. While the IPD meta-analysis can help avoid problems associated with the analyses and reporting of the component studies, it cannot eliminate bias due to their study design or conduct. For example, studies which recruited high-risk women will likely have higher incidence estimates. In addition, due to the variety of study designs, not all stratification subgroups may be available in all component studies. Second, as the HC-HIV meta-analysis dataset is a convenience sample of prospective longitudinal studies that were identified for an analysis of hormonal contraception and the risk of HIV acquisition, the studies included may not be representative of all populations in the regions of interest for the STI/BV analysis. Finally, it is also possible that we may be unable to recode variables appropriately across studies and may not be able to investigate all sub-classifications of interest.

We will perform the following sensitivity analyses to examine the robustness of the results of our meta-analyses:

1. Based on the type of diagnostic criteria – stratify and analyze data/studies by the following criteria :
2. For chlamydia and gonorrhea: any test vs. NAAT only
3. For BV: any test vs. Nugent/Ison-Hay only
4. Based on the assessment of the risk of bias of the component study – stratify studies with and without an identified risk of bias. Suggested stratification for incidence estimates: studies that have retention rates <80% at one year vs. studies that have ≥80% retention
5. Based on intervention arm – repeat incidence analysis excluding all intervention arms.
6. Based on length of follow-up – for calculation of incidence, stratify studies with short versus longer follow-up time periods. Suggested stratification: ≤3 months vs 3 or more months followup
7. Based on study inclusion criteria – remove studies that included diagnosis with a specific STI for study inclusion for investigation of the prevalence and incidence of other STIs (if resources allow)
8. Based on censoring criteria – for calculation of incidence do not censor at first diagnosis of STI in question (if resources allow)

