**Table 5. Planned tables and forest plots**

| **Analysis objective** |  | **Meta-analysis output/presentation** | | | |
| --- | --- | --- | --- | --- | --- |
|  | **Analysis population** | **Baseline table** | **Heterogeneity evaluation** | | **One-stage stratified analysis and two-stage random effect analysis** |
|  |  |  | **I^2^** | **Forest plot** |  |
| **Primary** |  |  |  |  |  |
| **To evaluate the prevalence of selected STIs/BV: gonorrhea, chlamydia, syphilis, trichomoniasis, HSV-2, and/or BV** | **All studies** | **√** | **√** | **√** | **√** |
|  | **Region**: South Africa, Eastern Africa, Southern Africa | **√** | **√** |  | **√** |
|  | **Population type**: higher-risk or clinic/community-based populations | **√** | **√** |  | **√** |
|  | **Time period**: baseline data were collected prior to 2002, during 2003 to 2006 2007 or later | **√** | **√** |  | **√** |
|  | **Age**: 15-49 years, 15-24 years, 25-49 years | **√** | **√** | **√** | **√** |
|  | **Pregnancy**: pregnancy status at baseline | **√** | **√** |  | **√** |
|  | **Cross-stratum (Region, Population type, Time period, Age, Pregnancy)**^1^ | **√** | **√** |  | **√** |
| **To evaluate the incidence of selected STIs: chlamydia, gonorrhea, and HSV-2** | **All studies** | **√** | **√** | **√** | **√** |
|  | **Region**: South Africa, Eastern Africa, Southern Africa | **√** | **√** |  | **√** |
|  | **Population type**: higher-risk or clinic/community-based populations | **√** | **√** |  | **√** |
|  | **Time period**: baseline data were collected prior to 2002, during 2003 to 2006 2007 or later | **√** | **√** |  | **√** |
|  | **Age**: 15-49 years, 15-24 years, 25-49 years | **√** | **√** | **√** | **√** |
|  | **Pregnancy**: pregnancy status at baseline | **√** | **√** |  | **√** |
|  | **Cross-stratum (Region, Population type, Time period, Age, Pregnancy)**^1^ | **√** | **√** |  | **√** |
| **Secondary** |  |  |  |  |  |
| **To evaluate the prevalence of co-infections of selected STIs/BV: gonorrhea, chlamydia, syphilis, trichomoniasis, HSV-2, and/or BV** | **All studies** |  | **√** |  | **√** |
| **To evaluate the incidence of co-infections among the STIs: chlamydia, gonorrhea, and HSV-2** | **All studies** |  | **√** |  | **√** |
| **Sensitivity Analysis** |  |  |  |  |  |
| **To evaluate the prevalence of gonorrhea, chlamydia, syphilis, and BV based on the type of diagnostic criteria** | **All studies** |  | **√** |  | **√** |

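### The time-period strata leave women with a 2002 baseline in no stratum, and Table 5 disagrees with the body text on the incidence outcomes and on pregnancy as an incidence stratifier.

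*Protocol*

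**What the plan says.** **Time period.** Section 3.6 bases time period on each woman's own baseline date. The earliest stratum is "participants whose baseline data were collected prior to 2002", the middle one "participants whose baseline data were collected during 2003 to 2006", and the latest "participants whose baseline data were collected in 2007 or later". Table 5 gives the same cut-points once under prevalence and once under incidence: "baseline data were collected prior to 2002, during 2003 to 2006 2007 or later". Section 3.6 allows the periods to be regrouped if sample size requires it. Section 2 names time period as a stratifier in both primary objectives.

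**Incidence outcomes.** Section 3.3 states that "incidence will be estimated for five of the selected STIs" and names chlamydia, gonorrhea, syphilis, trichomoniasis and HSV-2. Objective 2 names the same five in Sections 2 and 3.2. The primary incidence row of Table 5 reads "To evaluate the incidence of selected STIs: chlamydia, gonorrhea, and HSV-2", and the row for incident co-infection lists the same three. Section 5 describes Table 5 as summarising the planned tables and forest plots.

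**Pregnancy.** Among the individual-level stratifiers, Section 3.6 lists "pregnancy status (prevalence estimates only" with that restriction attached. Objective 2 as worded in Section 2 leaves pregnancy out. Objective 2 as worded in Section 3.2, the last paragraph of Section 5.2.1 and the incidence block of Table 5 all include it.

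**Optional analyses.** Section 5.3 suggests splitting studies by follow-up as "≤3 months vs 3 or more months followup". Section 3.7 gives an example grouping of the number of diagnoses: none, one, one to two, and three or more.

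**The concern.** A stratifier should place every participant in exactly one category. The time-period rule does not, and it serves both primary objectives. Because the same cut-points stand in 3.6 and twice in Table 5, a programmer who follows the protocol will build the gap into the prevalence and the incidence output alike. A programmer who notices it must choose a neighbour for 2002. Two choices are equally natural and give different strata. The HC-HIV dataset already exists, so an assignment not fixed in writing could be made after the estimates have been seen.

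The two Table 5 conflicts raise a different issue. A reader cannot tell from the protocol whether syphilis and trichomoniasis were left out of the incidence rows on purpose or by oversight, or whether incidence by baseline pregnancy is a planned analysis. Either ambiguity leaves room to decide what is reported once results are known.

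**Working it through.** No sample size, power or error rate is involved, so there is no figure of the plan's own to reproduce. The check is to code each category set literally, count how many categories hold each value, and compare the outcome lists.

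**1. Category sets**

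| Set (source) | Categories as written | Values not in exactly one category |
|---|---|---|
| Time period (3.6; Table 5, two rows) | year < 2002; 2003 to 2006; year ≥ 2007 | 2002: in none |
| Age (3.6) | 15-24; 25-49 (15-49 is the overall range) | none |
| Follow-up length (5.3) | ≤ 3 months; ≥ 3 months | exactly 3 months: in both |
| Number of diagnoses (3.7) | 0; 1; 1-2; 3 or more | 1: in two; 2 has no category of its own |

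The years 1990 to 2014 were tested, and 2002 is the only one that fails. If the first period is read as year ≤ 2002, no year fails. Starting the middle period in 2002 closes the gap equally well. The age list is sound, because 15-24 and 25-49 divide 15-49 without gap or overlap.

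**2. What a 2002 baseline loses**

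Region and population type are study-level characteristics, and age comes from the woman herself. None depends on the baseline year, so those estimates and the overall estimates keep these women. Only the time-period estimates, and the cross-strata that use time period, lose them.

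**3. How many women**

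The 26 rows of Table 1 sum to 37,681, in line with the roughly 37,000 in the study summary. Table 1 has no enrolment dates, and no other part of the protocol gives them by study. The number of women with a 2002 baseline therefore cannot be derived. In addition, Section 3.2 restricts the studies separately for each infection, so even the total of 37,681 is not the denominator of any one estimate.

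**4. Incidence outcomes**

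- Sections 2, 3.2 and 3.3: chlamydia, gonorrhea, syphilis, trichomoniasis, HSV-2 (5).
- Table 5, primary incidence and incident co-infection: chlamydia, gonorrhea, HSV-2 (3).
- Difference: 5 − 3 = 2, namely syphilis and trichomoniasis.

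Section 3.4 gives a two-part definition of incident syphilis and restricts incident trichomoniasis to studies using InPouch or NAAT. The body text therefore clearly intends both.

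**5. Pregnancy as an incidence stratifier**

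- Included: Objective 2 in Section 3.2; Section 5.2.1, which applies one list of strata to prevalence and incidence; Table 5, in its own incidence row and in the cross-stratum row.
- Not included: Objective 2 in Section 2, by omission; Section 3.6, by explicit restriction to prevalence.

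These statements cannot all hold.

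**The case against.** The strongest reply is that these are drafting slips with little reach. Section 3.6 already lets the periods be adjusted. Time period is explored only within region and population type, and no overall pooled estimate changes. Much of this is fair and limits the size of the point. But the adjustment clause is tied to sample size and does not say where 2002 belongs, so it does not repair the rule.

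Four stronger readings are tempting, and the documents do not support them.

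- *That a stated number of women is lost.* One could spread the Table 1 total over an assumed span of enrolment years. The protocol gives neither the span nor the spread, and the true count could be close to zero or large.
- *That syphilis and trichomoniasis incidence have no planned output.* Table 5 is a summary, and Section 3.6 refers to Supplemental Tables 2.1 and 2.2 for the incidence stratifications; these are not in the text at hand. What can be said is that the Table 5 rows disagree with the body.
- *That the first period was meant to include 2002.* The document does not settle which neighbour should take that year.
- *That incidence by baseline pregnancy would mostly describe time after the pregnancy.* This would need gestation at baseline and follow-up time per study, which the protocol does not give. The contradiction stands without it.

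The two overlaps are indeed minor. The follow-up split is only suggested, for a sensitivity analysis, and the diagnosis counts are an example for an analysis that depends on resources.

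**Conclusion.** The point holds for three items. First, the time-period rule is wrong as stated: it leaves one calendar year, 2002, in no stratum of a named stratifier of both primary objectives, in Section 3.6 and in two rows of Table 5. The effect is confined to time-period estimates and time-period cross-strata, and its size in women cannot be determined from the protocol. Second, the incidence and incident co-infection rows of Table 5 omit two of the five STIs that Sections 2, 3.2 and 3.3 name. Third, the protocol contradicts itself on whether incidence is stratified by pregnancy. The two overlapping category sets are minor.

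The first item assumes only that the strata are coded as written. The other two rest on a direct comparison of the sections. These are not details left for a statistical analysis plan, because the protocol itself states them, wrongly or inconsistently.

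**What to change.** Before analysis:

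1. Assign 2002 to one adjoining period, as either 2002 or earlier, or 2002 to 2006. The sponsor should state which, and use the same wording in Section 3.6 and in both time-period rows of Table 5.
2. List all five STIs in the incidence and incident co-infection rows of Table 5.
3. Reconcile pregnancy as an incidence stratifier across Sections 2, 3.2, 3.6 and 5.2.1 and Table 5. One way is to remove it from the incidence strata in 3.2, 5.2.1 and Table 5 (including the cross-stratum row), which agrees with Section 2 and Section 3.6. In 5.2.1 the shared list of strata would then need separate wording for prevalence and incidence.
4. As minor edits, make the suggested follow-up split ≤ 3 versus > 3 months, and the example diagnosis counts 0, 1, 2, 3+.

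The cost is wording only. No new data are needed.

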**2. OBJECTIVES**

Using individual level data from the 18 prospective, longitudinal studies included in the HC-HIV meta-analysis dataset, we will estimate the prevalence and incidence of selected STIs/BV among women in sub-Saharan Africa and investigate potential differences by region, population type, and demographic characteristics.

Specifically, we will investigate the following objectives:

1. To evaluate the prevalence of selected STIs (chlamydia, gonorrhea, trichomoniasis, syphilis, and HSV-2) and BV among women in sub-Saharan Africa by region, population type, time period, age, and pregnancy status.
   1. To evaluate the prevalence of co-infections among the STIs/BV
2. To evaluate the incidence of selected STIs (chlamydia, gonorrhea, syphilis, trichomoniasis,and HSV-2) among women in sub-Saharan Africa by region, population type, time period, and age.
   1. To evaluate the incidence of co-infections among the STIs

The term “STIs/BV” may refer to up to 6 conditions: gonorrhea, chlamydia, syphilis, trichomoniasis, HSV-2, and/or BV. For each objective, the precise conditions included were determined by the biological/ epidemiological basis for the particular research question, the availability of STI/BV-specific data at different time points, the validity of combining test results across studies or of calculating incidence for a given condition, and other methodological and biological considerations. See Section 3.3 for more details. Human papillomavirus (HPV) is not included as the majority of studies did not include HPV data.

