**5.2.1 Two-stage meta-analysis**

We will use two-stage meta-analysis as our primary approach to examine prevalence and incidence estimates. Using this method, participants in each study are compared directly only with other participants in the same study. The two-stage method is well suited to assess between study heterogeneity. While the method is less suitable for identifying prognostic factors (due to the different sets of covariates measured across datasets), it is possible to assess effect modification.

In the first stage, IPD in each study are analyzed separately to obtain summary statistics. We will use binomial regression models to estimate prevalence estimates for each selected STI/BV and Poisson regression to estimate the incidence for each selected STI.

If appropriate, the second stage is to use standard meta-analysis techniques to combine the summary measures to give an overall estimate of prevalence and incidence across studies by population-type. The decision to combine results and conduct further analyses using random and/or fixed effect models depends on the level of between-study heterogeneity.

The same approach will be used to estimate prevalence and incidence for each stratum of interest based on region, population type, age, pregnancy status, and time period of the study.

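### The time-period strata skip calendar year 2002, so a woman whose baseline fell in 2002 belongs to none of them

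*Protocol*

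**What the plan says.** Section 3.6 treats time period as an individual-level variable, set by the date of each woman's own baseline data. The first two categories read "collected prior to 2002 (“earliest” time period), participants whose baseline data were collected during 2003 to 2006". The third is "participants whose baseline data were collected in 2007 or later (“latest” time period". The section then adds one allowance: "The categorization of time periods may be adjusted if necessary based on available sample size".

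Table 5 lists time period under its primary heading twice, once for prevalence and once for incidence, with the same boundaries: "baseline data were collected prior to 2002, during 2003 to 2006 2007 or later". In each block it plans a baseline table, an I² evaluation and one- and two-stage estimates by period, and a cross-stratum row that includes period.

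Section 2 makes time period part of the objectives. Objective 1 asks for prevalence "among women in sub-Saharan Africa by region, population type, time period, age, and pregnancy status", and objective 2 also names time period for incidence. Section 5.2.1, listing the strata for the two-stage analysis, ends with "population type, age, pregnancy status, and time period of the study".

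**The concern.** A stratification rule should place every participant in exactly one stratum. This one has a hole of a full calendar year at its first boundary, and no other text in the protocol assigns that year.

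Two things can follow if any woman has a 2002 baseline. A programmer who codes the rule as written leaves her without a period, and the period-specific numbers then do not add up to the total. A programmer who notices the hole has to choose a side, and the protocol does not show which side was meant. If that choice is made after results have been seen, it decides which women form the earliest and the middle groups, and pre-specified categories are meant to prevent that.

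**Working it through.** **Inputs.** The three categories come from Section 3.6 and are repeated in Table 5. Let y be the calendar year of a woman's baseline.

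- Earliest: y < 2002, that is y ≤ 2001
- Later: 2003 ≤ y ≤ 2006
- Latest: y ≥ 2007

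**Coverage check.** Each year from 1980 to 2019 was tested against the three conditions.

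| Baseline year | Strata that it meets |
| --- | --- |
| 2001 and before | earliest |
| 2002 | none |
| 2003 to 2006 | later |
| 2007 and after | latest |

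2002 is the only year with no stratum, and no year falls in two.

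**Does another passage close the gap?** Table 5 repeats the boundaries and so repeats the gap, in both blocks. The allowance in Section 3.6 lets the team redraw categories because of sample size; it does not say where 2002 goes. Sections 2 and 3.2 name time period without defining it.

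**Which results are exposed?** Only those that use the variable: the time-period rows of Table 5 and the cross-strata that include period. The all-studies, region, population-type, age and pregnancy rows do not depend on it.

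**How many women?** The study summary states about 37,000. The 26 rows of Table 1 add to 37,681, which is 681 more (681 / 37,000 = 1.8%), so the stated total is reproduced. The share with a 2002 baseline cannot be derived, because neither Table 1 nor any other part of the protocol gives enrolment dates. As pure assumption, a share of 1% would be 0.01 × 37,681 = 377 women and a share of 20% would be 0.20 × 37,681 = 7,536. Nothing in the protocol favours any value in that range, or excludes zero.

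**Do the two obvious repairs work?**

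- 2002 or earlier / 2003 to 2006 / 2007 or later: every year falls in exactly one stratum.
- Before 2002 / 2002 to 2006 / 2007 or later: every year falls in exactly one stratum.

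**The case against.** The best defence is that this is one boundary slip copied into a summary table, in categories that the protocol itself treats as provisional. Period is also second in order: Section 3.6 stratifies first by region and population type and explores period within those strata. Section 5.1 requires descriptive analyses before any meta-analysis, so unclassified women might well be noticed. Perhaps no woman was enrolled in 2002 at all. The supplemental tables of proposed stratifications, to which Section 3.6 refers, are not in the text at hand and were not checked.

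Much of this stands, and it limits the weight of the point. It does not remove the point. Whether the cause is a slip or a decision, the text fixes the categories with a gap. Noticing the gap during descriptive work still leaves an undefined choice, and the sample-size allowance gives no ground for making it either way. If there were no 2002 baselines, the correction changes no result.

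A reader might also take the phrase in Section 5.2.1 as a rival, study-level definition of period. The documents do not support that. Section 3.6 lists time period of enrolment among the individual-level characteristics and defines it by each participant's baseline date. The wording in 5.2.1 is loose shorthand in a list.

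**Conclusion.** The point holds: as written in Section 3.6 and in both primary blocks of Table 5, a 2002 baseline has no time-period stratum. The consequence is confined to period estimates and to cross-strata that use period, and it arises only if some women were enrolled in 2002. Their number is unknown and may be zero. This is a should-fix item, not a threat to the main estimates.

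Three stronger readings are tempting and are not supported.

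- A reader might put the loss at 5.0% to 6.7% of women by spreading Table 1 evenly over 15 to 20 years (37,681 / 20 = 1,884; 37,681 / 15 = 2,512). Nothing in the protocol supports even enrolment. The dataset combines 18 separate studies, with single rows as large as 5,567 and 5,654 women, so enrolment could be very uneven across years. Section 3.2 also applies inclusion criteria separately for each infection and restricts intervention arms for incidence, so 37,681 is not the analysis set for any one estimate.
- A reader might say that a comparison of the earliest with the later period is biased. The protocol plans estimates within periods and defines no named contrast or test between them.
- A reader might say that women are already known to be missing. Without enrolment dates, that cannot be said.

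**What to change.** Before any period estimates are run, assign 2002 to one stratum and use the same wording in Section 3.6 and in both Table 5 blocks. Either closure serves: 2002 or earlier, 2003 to 2006, 2007 or later; or before 2002, 2002 to 2006, 2007 or later. The protocol does not show which was intended, so the study team should choose without reference to the period results and record the choice. If the supplemental stratification tables carry the same boundaries, change them too.

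As a minor alignment, let Section 5.2.1 refer to the period of the participant's baseline visit.

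The cost is a few words in three places and no new data. A count of women by baseline year, made when the analysis file is built, would show whether anyone is affected.
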